### Anesthesia induction and intervention

After preoxygenation, general anesthesia will be induced with intravenous sufentanil (0.2–0.3 μg/kg), etomidate (0.1–0.2 mg/kg), and rocuronium (0.6 mg/kg). An i-gel supraglottic airway will be inserted, and mechanical ventilation will be commenced.

Hemodynamic management will begin immediately post-induction. In the individualized management group, a continuous peripheral intravenous infusion of norepinephrine (10 μg/mL) will be started at 0.02 μg/kg/min and titrated to maintain SBP within ± 10% of the baseline, with a maximum dose of 0.2 μg/kg/min. In the standard management group, intermittent intravenous boluses of norepinephrine (10 μg) will be administered as rescue therapy only if hypotension occurs (defined as SBP < 90 mmHg or a > 30% decrease from baseline). For all patients, the MAP will be maintained at ≥ 65 mmHg as a universal minimum target [17]. If target blood pressure cannot be maintained at the maximum dose, rescue therapy (e.g., dopamine 2–5 μg/kg/min or epinephrine 0.01–0.05 μg/kg/min) will be initiated based on real-time hemodynamic monitoring. Finally, an ultrasound-guided supra-inguinal fascia iliaca compartment block (S-FICB) with 35 mL of 0.25% ropivacaine will be performed on the surgical side for postoperative analgesia.

### Anesthesia maintenance

Anesthesia will be maintained with sevoflurane titrated to a BIS value of 40–60. Mechanical ventilation will be set to a tidal volume of 8 ml/kg with respiratory rate adjusted to maintain end-tidal CO₂ between 35–45 mmHg. Supplemental bolus doses of rocuronium, sufentanil, and remifentanil may be administered as needed.

GDFT will be guided by the LiDCOrapid system. A fluid challenge of 250 mL lactated Ringer’s solution will be administered over 10 min; an increase in SV of ≤ 10% will be considered indicative of fluid non-responsiveness, establishing the optimal SV. SVV will be maintained at ≤ 13% throughout surgery (S2 Appendix).

### Recovery of anesthesia

At the end of surgery, anesthetic administration is terminated and the patient is transferred to the postanesthesia care unit (PACU), where the same intraoperative hemodynamic management strategy is maintained. The laryngeal mask airway is removed once the patient responds to commands and demonstrates adequate spontaneous ventilation. Pharmacologic reversal agents are administered if indicated for persistent respiratory depression. Patients will be observed for at least 30 min after extubation and must achieve a modified Aldrete score of ≥ 9 before discharge to the ward.

### Postoperative analgesia

Upon ward or ICU admission, a standardized intravenous patient-controlled analgesia (PCA) protocol is initiated. The PCA solution contains sufentanil 1 µg/mL (100 µg diluted in 100 mL normal saline) and is programmed with a basal infusion of 2 mL/h, a bolus dose of 2 mL, and a 15-min lockout interval. Nurses instruct patients to self-administer boluses for breakthrough pain (NRS > 3). Respiratory rate, sedation level, and pain intensity are monitored and documented at 4-h intervals to ensure safety.

## Outcome

### Primary outcome

The primary outcome is a composite of at least one organ system dysfunction (including respiratory, cardiovascular, renal, and nervous system) in patients within 7 days after surgery. The occurrence and severity of organ dysfunction should be assessed daily and evaluated during follow-up assessments (For specific definitions of organ system dysfunction, please refer to the S1 Appendix).

### Secondary outcomes

The secondary outcomes encompass the components of the primary outcome, other postoperative clinical events (including systemic inflammatory response, infection, and thromboembolic events), intraoperative variables (hemodynamic data, fluid balance, and serum lactate levels), postoperative recovery measures (pain score, durations of ICU and hospital stay), and all-cause mortality within 30 days after surgery. More details are provided in the S2 Appendix.

Hemodynamic variables, collected from anesthesia induction until PACU discharge, will consist of the total dosage of norepinephrine administered; the incidence of intraoperative hypotension (defined as SBP < 90 mmHg or a decrease > 30% from baseline, or MAP < 65 mmHg); the total dosage of urapidil administered; the incidence of intraoperative hypertension (defined as SBP > 160 mmHg and/or diastolic blood pressure > 90 mmHg) [15]; and the occurrence and management of severe bradycardia (defined as heart rate < 40 beats per minute).

### Follow-up procedures

To ensure a comprehensive evaluation of the primary outcome within 7 days after surgery, a structured follow-up and data collection procedure will be implemented (Table 1). Blood samples are planned to be collected from all patients on postoperative days 1, 2, and 7. For patients discharged earlier, detailed guidance and assistance will be provided to facilitate their return for clinical assessment and blood sampling on day 7. If an in-person return is not possible, a blinded assessor will conduct a structured telephone interview to collect information on clinical symptoms. Concurrently, laboratory test results that are routinely available from other healthcare institutions during this period will be collected. The primary composite outcome will be adjudicated based on all clinical and laboratory data obtained up to postoperative day 7.

### Adverse events

Adverse events (AEs) primarily include respiratory depression, bradycardia, nausea and vomiting, chills, anaphylactic shock, and cardiac arrest. Any unexpected AEs occurring during the trial will be promptly managed. In the event of a serious adverse event (SAE), regardless of its relationship to the intervention, the investigator will document it in detail in the source records, complete the case report form (CRF), and sign and date the entries contemporaneously.

### Data collection and management

All participants will be evaluated at baseline. All data will be collected using paper-based CRFs. Hard copies of the CRFs will be stored in locked cabinets with restricted access. Data from the CRFs will be entered into a secure electronic database. Access to the database will be limited to authorized study personnel who have signed a confidentiality agreement. All participant personal information will be de-identified and kept strictly confidential throughout the study. Anonymized datasets may be made available for secondary research purposes upon reasonable request to the corresponding author and with approval from the institutional review board.

### Sample size estimation

The sample size calculation was based on the primary composite outcome of postoperative organ dysfunction. A previous cohort study reported incidences of 51.7% *vs*. 38.1% for standard and individualized management, respectively [15]. However, the particularly high vulnerability of older hip fracture patients is demonstrated by elevated rates of intraoperative hypotension (approximately 60%) [18], postoperative AKI (7.6% to 11.3%) [18–20], and myocardial injury (14%) [18], we anticipate a higher baseline risk in our standard care group and a potentially larger treatment effect.

Therefore, to ensure the study is adequately powered to detect a conservative and clinically significant effect, we assumed a 55% incidence of the primary outcome in the standard management group and a 30% incidence in the individualized management group. Using a chi-square test in PASS 15 software with a two-sided α of 5% and 90% power, a minimum sample size of 82 patients per group was calculated. To account for an anticipated 10% dropout rate, a total of 180 patients (90 per group) will be enrolled. This calculation employs a conservative effect size estimate, anticipating a higher baseline risk of organ dysfunction in our frail older hip fracture population compared to the referenced study in major abdominal surgery [15], thereby ensuring adequate power to detect a clinically meaningful difference.

### Statistical analysis

All analyses will be performed using SPSS (version 25.0; IBM Corp., Armonk, NY, USA). A two-sided *P*-value < 0.05 will be considered statistically significant. The primary outcome will be compared between groups using the chi-square test. To account for potential baseline imbalances, the primary analysis will be supplemented with a multivariable logistic regression model adjusting for age (as a continuous variable) and ASA physical status classification. The normality of continuous data will be assessed using the Shapiro–Wilk test. Continuous variables will be summarized as means with standard deviations or medians with interquartile ranges and compared using the independent samples t-test or the Mann–Whitney U test, as appropriate. Categorical variables will be presented as numbers (percentages) and compared using the chi-square test or Fisher’s exact test.

For secondary analyses, the relationships between the intervention and the primary outcome will be further explored using multivariable logistic regression, adjusting for key baseline covariates. Repeated-measures data (e.g., SBP over time) will be analyzed using generalized estimating equations. Time-to-event data will be analyzed with the Kaplan–Meier method and the log-rank test. The ITT principle will be applied for all analyses. Any missing data will be handled using complete-case analysis.

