### Randomization and blinding

Eligible participants will be randomly allocated in a 1:1 ratio to either the individualized or standard management group. The randomization sequence will be computer-generated by an independent statistician using block randomization with varying block sizes (of 4 and 6), stratified only by age group (65–74 years vs. 75–85 years) to ensure balance across this key prognostic factor. To guarantee allocation concealment and balance between groups throughout the trial, sequentially numbered, opaque, sealed envelopes will be used. The envelopes will be stored by an independent coordinator and opened by the attending anesthesiologist immediately prior to anesthesia induction. Due to the nature of the intervention, the anesthesiologist performing the intervention cannot be blinded. However, participants, postoperative outcome assessors, and data analysts will remain blinded to group assignment throughout the trial.

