## Intervention

### Preoperative interview

Within 24 h prior to surgery, eligible patients will undergo a comprehensive preoperative assessment. This includes evaluation of general status, medical history, physical examination, and laboratory results to determine ASA physical status and Clinical Frailty Scale (CFS) score. The study's purpose, procedures, risks, and benefits will be explained in detail to the patient and their legally authorized representative. Written informed consent for both routine anesthesia and trial participation will be obtained.

The reference blood pressure will be obtained under standardized, pain-stabilized conditions. On the day before surgery, after achieving effective analgesia (Numerical Rating Scale [NRS] score ≤ 3) with Flurbiprofen Cataplasms (initiated upon admission and supplemented with rescue opioids as needed), the patient will rest supine for 5 min. Three consecutive SBP measurements will then be taken at 2-min intervals. If the variation between any two readings exceeds 10%, the series will be repeated after an additional 5-min rest. The mean of three stable measurements will be recorded as the reference SBP.

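### Randomisation is stratified by age group, but the primary test ignores age: a mildly conservative choice that costs about 0 to 2 points of power and could be improved without new data

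*Protocol article*

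**What the plan says.** All references are to the protocol article.

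- **Randomization and blinding.** Blocks of 4 and 6 are permuted within two age groups, 65–74 and 75–85 years. Age group is the only stratification factor, and the stated purpose is "to ensure balance across this key prognostic factor".
- **Statistical analysis.** "The primary outcome will be compared between groups using the chi-square test". To deal with possible baseline imbalance, "the primary analysis will be supplemented with a multivariable logistic regression model adjusting for age (as a continuous variable) and ASA physical status classification". A further logistic regression on key baseline covariates, not listed, is a secondary analysis. Categorical variables are shown as counts and percentages.
- **Preoperative interview.** Before surgery every eligible patient is assessed using "laboratory results to determine ASA physical status and Clinical Frailty Scale (CFS) score" among other information, so both scores exist at baseline.
- **Sample size estimation.** The trial is sized on the same unadjusted test: "Using a chi-square test in PASS 15 software with a two-sided α of 5% and 90% power". The rates are 55% and 30%, and "a minimum sample size of 82 patients per group was calculated".

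**The concern.** Stratified blocks force the arms to be nearly equal on age group. If age affects the outcome, this removes the part of the chance difference between arms that age imbalance would otherwise cause. The plain chi-square test still counts that part in its variance. Its standard error is then slightly too large, it rejects too seldom under the null, and it loses some power. The age-adjusted model would recover this, but it does not decide the trial.

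The reason given for that model, possible imbalance, is the weaker one: stratification already limits imbalance in age. The better reason is precision, and it applies to the primary analysis. What is at stake is a small amount of power that could be had from data already collected.

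**Working it through.** **1. The plan's own figure.** Inputs from Sample size estimation: rates 0.55 and 0.30, two-sided α 0.05, power 0.90. With pooled variance under the null and no continuity correction:

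n = [1.960·√(2·0.425·0.575) + 1.282·√(0.55·0.45 + 0.30·0.70)]² / 0.25² = (1.370 + 0.867)² / 0.0625 = 80.1, so 81 per group.

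The stated 82 is reproduced to within one patient. Power at 82 per group is Φ[(0.25·√82 − 1.370)/√0.4575] = Φ(1.321) = 90.7%. With 10% dropout from 180, 162 patients remain (81 per group) and power is 90.3%. The planned power therefore does not depend on any adjustment.

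**2. Type I error of the chi-square test.** The document gives no association between age and outcome, so the odds ratio for 75–85 vs 65–74 years is assumed to lie between 1 and 4, with half the patients in each stratum. Take a common event rate of 42.5%, the mean of 55% and 30%. The chi-square test uses the variance 0.425·0.575 = 0.2444. With the strata balanced, the true variance is the average within-stratum variance. The test statistic is thus shrunk by the square root of the ratio of the two:

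| Age OR | Risk, younger / older | Within-stratum variance | Ratio | Type I error = 2·[1 − Φ(1.960/√ratio)] |
|---|---|---|---|---|
| 1 | 0.425 / 0.425 | 0.2444 | 1.000 | 5.0% |
| 2 | 0.341 / 0.509 | 0.2374 | 0.971 | 4.7% |
| 3 | 0.294 / 0.556 | 0.2273 | 0.930 | 4.2% |
| 4 | 0.263 / 0.587 | 0.2180 | 0.892 | 3.8% |

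The simulation in step 3 agrees.

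**3. Chi-square against an age-stratified Cochran-Mantel-Haenszel (CMH) test.** These come from 200,000 simulated trials per scenario with 82 per group. Overall risks are fixed at 55% and 30% for power and at 42.5% in both arms for type I error.

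| Age OR | Power, chi-square | Power, CMH | Type I error, chi-square | Type I error, CMH |
|---|---|---|---|---|
| 1 | 90.4% | 90.5% | 4.8% | 4.8% |
| 1.5 | 90.3% | 90.5% | 4.7% | 4.8% |
| 2 | 90.5% | 91.2% | 4.6% | 4.9% |
| 3 | 90.8% | 92.4% | 4.1% | 4.9% |
| 4 | 91.2% | 93.4% | 3.7% | 5.0% |

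The gain from stratifying is below 1 point up to an odds ratio of 2, and 1.6 to 2.2 points at 3 to 4. With 60% of patients in the older stratum the results are nearly the same.

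**4. Adding further covariates.** Logistic regression on continuous age and ASA class was compared with the chi-square test in 4,000 runs per scenario. Half the patients were assumed to be ASA III, with mean age 76 and SD 6. Power rose from 90.7% to 90.9% when both odds ratios were 1.5 (age per 10 years), from 90.7% to 91.9% when both were 2, and from 90.1% to 93.3% when both were 3. If a frailty score is added with an assumed odds ratio of 1.8 to 2.7 per SD, and an age-stratum odds ratio of 2.2 to 3.3, the total gain is about 2 to 5 points. None of these associations is in the document.

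**5. Effect measure.** At the planned rates the risk difference is 25 points, the risk ratio is 0.30/0.55 = 0.55, and the odds ratio is (0.30/0.70)/(0.55/0.45) = 0.35. With an outcome this common, an odds ratio reported alone can be misread as a larger relative reduction.

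**The case against.** The strongest reply is that nothing is invalid. The test errs on the safe side, the trial was sized on the test it will use, and that test reaches 90%. All of this stands, and it limits the point to efficiency.

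Three stronger readings are tempting and the document does not support them.

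- **That the mismatch wastes substantial power.** Age alone is worth about 0 to 2 points. The larger gains come from an assumed effect of frailty, which is not a stratification factor. Nor does adjustment settle whether 55% vs 30% is a realistic effect; that is a separate sample-size question.
- **That the plan yields no effect estimate.** This is true of the chi-square test taken alone, but not of the plan. The supplementary model gives an adjusted odds ratio, and the reported percentages give both arms' risks. The effect measure and its interval may also be in an analysis plan that is not shown.
- **That leaving the Clinical Frailty Scale out of the named model is an error.** It contradicts nothing in the article, and the scale may be among the unlisted covariates of the secondary model.

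It is also fair to object that recruitment is under way, with completion due by June 2026, so a change to a published primary analysis comes late. That is a real cost. It is manageable only if the change is made and dated before anyone sees outcomes by arm.

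**Conclusion.** The point holds as a modest efficiency gain. The article names age a key prognostic factor and stratifies on it, then fixes a primary test that does not use it. Under assumed age odds ratios from 1 to 4, type I error falls from about 4.8% to 3.7% and the power forgone at 82 per group is about 0 to 2 points. If age is not prognostic, nothing is lost. Adjusting for ASA class and the Clinical Frailty Scale as well could be worth a few more points, conditional on associations that the document does not report. The direction is certain once age is prognostic; the size rests on these assumptions. A significant chi-square result would not be undermined by any of this.

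**What to change.** - **Primary analysis.** Name one prespecified age-adjusted analysis: logistic regression on treatment, age (continuous or as the randomisation stratum), ASA class and Clinical Frailty Scale. Use the CMH test by age stratum as the fallback if the model does not converge. Fix the coding of ASA class and the frailty scale in advance. The planned rates imply about 82·0.55 + 82·0.30 ≈ 70 events, enough for a model of this size.
- **Reporting.** Give the standardised risk difference and risk ratio with 95% CI from that model, alongside any odds ratio.
- **Chi-square test.** Keep it as a supportive analysis, so that the published plan can still be followed.
- **Timing.** Date and record the change before database lock, while analysts are blinded.

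The costs are a documented departure from the published primary analysis, and possibly a tool outside the SPSS menus for the standardised estimates. No new data or patients are needed. Missing data are to be handled by complete-case analysis, so a missing covariate would drop a patient; ASA class and the frailty score should be checked for completeness before lock.

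### The supplementary logistic model of the primary outcome names only age and ASA; the Clinical Frailty Scale and reference SBP, both recorded before allocation, should be added (minor)

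*Protocol article*

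**What the plan says.** Under Statistical analysis, the main comparison is unadjusted: "The primary outcome will be compared between groups using the chi-square test". The role of the adjusted model is stated next: "To account for potential baseline imbalances, the primary analysis will be supplemented with a multivariable logistic regression model". It is specified as a "multivariable logistic regression model adjusting for age (as a continuous variable) and ASA physical status classification". Later in the section, the relation between intervention and primary outcome is to be "further explored using multivariable logistic regression, adjusting for key baseline covariates"; those covariates are not listed. SBP over time is given as an example of repeated-measures data for generalized estimating equations (GEE). Missing data are handled by complete-case analysis.

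Under Preoperative interview, the assessment within 24 h before surgery serves "to determine ASA physical status and Clinical Frailty Scale (CFS) score". For blood pressure on the day before surgery, "The mean of three stable measurements will be recorded as the reference SBP". Under Randomization and blinding, allocation is stratified by age group alone (65–74 vs 75–85 years), and the envelope is opened just before induction. Sample size estimation refers to a "higher baseline risk of organ dysfunction in our frail older hip fracture population".

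**The concern.** A model meant to handle baseline imbalance does most good with prognostic variables that the randomisation does not balance. Of the two named covariates, age is already controlled in two bands by the stratification, and eligibility limits ASA to grades I–III. CFS and reference SBP have no such protection. Both are measured before allocation, so adjusting for them is valid. Reference SBP also sets the pressure target in one arm and the relative trigger in the other.

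If either variable predicts organ dysfunction, leaving it out lets a chance difference between arms pass into the adjusted estimate and gives up some power in the adjusted test. What is at stake is how well the supporting analysis does its stated job. The main test is not affected.

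**Working it through.** **1. Timing.** CFS: within 24 h before surgery. Reference SBP: the day before surgery. Envelope: immediately before induction. Both are baseline variables.

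**2. The plan's own sample size.** Inputs from Sample size estimation: 55% vs 30%, two-sided 5%, 90% power. The pooled proportion is (0.55 + 0.30)/2 = 0.425.

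n per group = [1.960·√(2·0.425·0.575) + 1.2816·√(0.55·0.45 + 0.30·0.70)]² / 0.25² = (1.370 + 0.867)² / 0.0625 ≈ 80.1, so 81.

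The article states 82, which agrees within one patient. Power at 82 per group is 90.7%. This is the power of the unadjusted test, and no covariate list enters it.

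**3. Size of a chance imbalance.** With 82 per arm, the difference in mean CFS in SD units has standard error √(2/82) = 0.156. One trial in 20 exceeds 1.96 × 0.156 = 0.31 SD in either direction. At an *assumed* log-odds of 0.7 per SD, that moves the treatment log odds ratio by about 0.31 × 0.7 ≈ 0.21, before age and ASA absorb part of it. The design effect is ln(0.30/0.70) − ln(0.55/0.45) = −1.05.

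**4. Power of the adjusted test, CFS added.** Simulation, 82 per arm, 3,000 trials per scenario. Assumed: log-odds 0.3 per SD for age and 0.5 for ASA III; correlation 0.4 of CFS with age and with the score underlying ASA. Each cell is power with age + ASA → with CFS added.

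| CFS log-odds per SD | 55% vs 30% (design) | 55% vs 37% (assumed) | 51.7% vs 38.1% (cited cohort) |
|---|---|---|---|
| 0.4 | 92.3 → 92.8% | 66.2 → 67.7% | 44.7 → 44.6% |
| 0.7 | 92.6 → 94.3% | 68.9 → 72.2% | 45.2 → 48.5% |
| 1.0 | 93.7 → 96.2% | 69.3 → 74.4% | 46.5 → 50.7% |

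With no prognostic value for CFS, the change is within 0.1 point. A run at 81 per arm (4,000 trials) agrees: from about 92.6% to 92.9%, 94.2% and 95.2% at the design effect; from 66–69% to 68%, 72% and 75% at 55% vs 37%. When reference SBP is also given prognostic value, the gain at the smaller effects reaches 6 to 7 points.

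**5. CFS and reference SBP both added, design effect.** Simulation, 82 per arm, 4,000 trials. Assumed odds ratios per SD: age 1.4, ASA 1.5; CFS correlated 0.3 with each.

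| Assumed OR per SD: CFS, SBP | Power, age + ASA → both added |
|---|---|
| 1.0, 1.0 | 92.6 → 92.7% |
| 1.3, 1.0 | 93.4 → 93.6% |
| 1.5, 1.2 | 93.5 → 94.1% |
| 2.0, 1.2 | 94.0 → 95.7% |
| 2.0, 1.5 | 94.8 → 96.2% |

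The standard error of the log odds ratio rises in every row (0.351 to 0.356 in the first, 0.364 to 0.396 in the last), as expected for a non-collapsible measure. Any power gain comes from the conditional log odds ratio moving further from zero (−1.234 to −1.396 in the last row). The variance of the standardised risk difference changes by +1.5% in the first row and −6% in the last.

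**The case against.** The strongest reply is that nothing here is an error. Age and ASA are a defensible prespecified pair. Age is the one variable that the article calls a key prognostic factor, adjusting for a stratification factor is standard practice, and continuous age captures variation within the two bands. The article does not show that CFS or reference SBP predicts the composite: frailty appears in the sample-size text only as a description of the population, and setting a treatment threshold does not make a variable prognostic. All of this stands, and it is why the point is minor.

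A reader might go further in three ways that the article does not support:

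- **That the primary analysis loses power.** It does not. The primary test is the unadjusted chi-square and the trial is sized for it.
- **That CFS and reference SBP are used in no analysis.** This is not established. They are in no *named* model, but the later regression has an unlisted covariate set that could include them.
- **That covariates will be picked after the results are seen.** The article does not say so. It condenses a fuller protocol, and a statistical analysis plan that is not shown may give the list. That regression is already placed among the secondary, exploratory analyses.

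Adding covariates also has a cost. Under complete-case analysis, a missing CFS or SBP value removes the patient from the model. As a guide, chi-square power falls from 90.7% at 82 per group to 90.0% at 80, so a few missing values could cancel a gain at the low end of the range.

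**Conclusion.** The point holds as a minor improvement to a supporting analysis. The supplementary model is there to account for baseline imbalance, yet it leaves out two baseline measurements that are already taken in every patient and that the randomisation does not balance. Under the assumed strengths, adding them raises the power of the adjusted test by about 0 to 3 points at 55% vs 30% and by up to about 7 points at smaller effects. The gain is nil if they are not prognostic, and no scenario showed a meaningful loss with complete data. The upper figures need a strong CFS effect (log-odds 1.0 per SD, an odds ratio of about 2.7) and a smaller treatment effect than the trial is designed for. The chi-square test and the 82 per group are unchanged.

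**What to change.** In Statistical analysis, before unblinding, specify the supplementary logistic model of the primary outcome as arm, age (continuous), ASA, CFS and reference SBP. In the GEE analysis of SBP over time, include reference SBP as a covariate.

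The cost is a sentence or two of analysis text, with no extra patients, visits or measurements. To limit the complete-case loss, check that both values are on the case report form for every patient before allocation.

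### The planned GEE of SBP over time names no baseline term; adding each patient's reference SBP would sharpen the arm comparison and let it be read against the ±10% band (minor)

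*Protocol article*

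**What the plan says.** All references are to the protocol article.

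- **Statistical analysis:** "Repeated-measures data (e.g., SBP over time) will be analyzed using generalized estimating equations". No scale, covariate or working correlation is given for this model. Age and ASA status are named as covariates only for the regression that supplements the primary outcome.
- **Preoperative interview:** supine SBP is measured the day before surgery, after pain control. "The mean of three stable measurements will be recorded as the reference SBP".
- **Anesthesia induction and intervention:** in the individualized arm norepinephrine is "titrated to maintain SBP within" 10% either side of baseline. In the standard arm the trigger is SBP below 90 mmHg or a fall of more than 30% from baseline. Both arms share a MAP floor of 65 mmHg. No other baseline SBP is defined, so I take baseline here to mean the recorded reference SBP.
- **Randomization and blinding:** allocation is "stratified only by age group", so reference SBP is not balanced by design.
- **Secondary outcomes:** hypotension is defined as SBP below 90 mmHg, a fall of more than 30% from baseline, or MAP below 65 mmHg. Hypertension is defined by absolute limits only (SBP above 160 and/or diastolic above 90 mmHg).

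**The concern.** The intervention is tied to the patient's own starting pressure, but the longitudinal analysis names SBP itself. The same reading then means different things in different patients. For a reference of 125 mmHg the ±10% band runs from 112.5 to 137.5, so 120 mmHg lies inside it. For a reference of 160 mmHg the band runs from 144 to 176, and 120 mmHg is 25% below reference.

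Two things follow if reference SBP is left out:

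1. Differences between patients in starting pressure, which the strategies do not change, stay in the residual variance and widen the confidence interval for the arm difference.
2. A mean difference in mmHg does not show where either arm sat relative to the ±10% band. The listed hypotension and hypertension outcomes do not show it either, because neither uses that band.

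This analysis is a process measure. Its use is to show how far the two strategies separated pressure, which readers will want to know above all if the primary result is null.

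**Working it through.** **The plan's own figure.** The protocol states no precision or power for the SBP analysis. Its one calculation concerns the primary outcome: "we assumed a 55% incidence of the primary outcome in the standard management group and a 30% incidence in the individualized management group", giving "90% power, a minimum sample size of 82 patients per group was calculated". The pooled-variance formula gives n = [1.960·√(2·0.425·0.575) + 1.2816·√(0.55·0.45 + 0.30·0.70)]² / 0.25² = 80.1, so 81 per arm. That agrees with 82 to within one patient. The point here does not touch it. I use the planned enrolment of 90 per arm below. With 82 per arm every standard error would be √(90/82) = 1.05 times larger.

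**Assumptions (none of these is in the documents).** Mean reference SBP μ = 140 mmHg, with SD s = 12 to 20 mmHg. Intraoperative SBP averages 97% of reference in the individualized arm and 85% in the standard arm. The between-patient SD of that ratio is 4 and 8 percentage points. I work with each patient's mean SBP, which stands in for a GEE arm effect averaged over time, and treat noise between five-minute readings as averaged out.

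**Formula.** For an arm with mean ratio f and ratio SD σ, the between-patient variance of mean SBP is f²s² + σ²(μ² + s²). The first term comes from reference SBP and is essentially removed by adjustment. The second remains.

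**Worked case, s = 18.**
- Individualized: 0.97²·324 + 0.04²·(19,600 + 324) = 304.9 + 31.9 = 336.7
- Standard: 0.85²·324 + 0.08²·19,924 = 234.1 + 127.5 = 361.6
- SE unadjusted: √[(336.7 + 361.6)/90] = 2.8 mmHg
- SE adjusted: √[(31.9 + 127.5)/90] = 1.33 mmHg

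**Across the range** (simulation, 4,000 replicates, reference SBP clipped to 90–179 mmHg in keeping with the exclusion at 180):

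| Reference SD (mmHg) | SE unadjusted | SE adjusted | Variance ratio | 16.8 mmHg in unadjusted SEs |
|---|---|---|---|---|
| 12 | 2.11 | 1.33 | 2.5 | 8.0 |
| 15 | 2.44 | 1.33 | 3.4 | 6.9 |
| 18 | 2.76 | 1.33 | 4.3 | 6.1 |
| 20 | 2.98 | 1.33 | 5.0 | 5.6 |

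The assumed separation is (0.97 − 0.85)·140 = 16.8 mmHg, so it is clear even without adjustment.

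**When precision would matter.** I repeated this with a wider set of assumptions: reference SD 10 to 25 mmHg, ratio SD 5 to 10 points in both arms, average ratio 0.93. Power is taken as Φ(difference/SE − 1.96).
- For reference SD 20 and ratio SD 8 points, the unadjusted SD is √[(0.93·20)² + 0.08²·(19,600 + 400)] = 21.8 and the SE is 21.8·√(2/90) = 3.25 mmHg. In simulation the adjusted SE is 1.7 mmHg.
- At 5% separation (7 mmHg) power is 58% unadjusted, 98% adjusted and 98.5% on the percentage scale. At 10% (14 mmHg) it is 99%, 100% and 100%.
- Over the whole range, unadjusted power is 41–98% at 5% separation and 93–100% at 10%. On the percentage scale it is 92–100% at 5% and about 100% at 10%.
- Reference SBP accounts for 31–91% of the between-patient variance of mean SBP.

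**Validity.** In simulations at ratio SD 8 points and reference SD 15 to 25, the unadjusted estimate is unbiased and its type I error is 5–6%.

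**The case against.** The best case against the point is that the article gives SBP over time only as an example and is silent on scale and covariates. A GEE with reference SBP as a covariate, or with percentage of reference as the outcome, would not contradict it. A condensed article may leave such detail to an analysis plan, and Secondary outcomes sends further detail to the S2 Appendix, which is not shown. This stands to the extent that the point must be conditional: it describes what happens if the model is run on SBP as named. It does not make the improvement less worthwhile.

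A reader might also infer four stronger things, which the documents do not support.

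- *Between-patient spread swamps the comparison.* It does not. Under the assumptions above the arm difference is 5.6 to 8 unadjusted standard errors. Only a separation near 5% of reference is at risk.
- *Chance imbalance in reference SBP biases the result.* Under randomization it is random error that the standard error already contains. At s = 18 a one-SE imbalance is 18·√(2/90) = 2.7 mmHg. Multiplied by the mean ratio of 0.91 it moves the SBP difference by 2.4 mmHg, and √(2.4² + 1.33²) = 2.8 mmHg is the unadjusted SE itself. Quoting both would count one thing twice.
- *Both arms are managed on purely relative limits.* The standard arm also has an absolute trigger, which is reached first when reference SBP is below 90/0.7 = 128.6 mmHg, and the MAP floor is absolute for everyone. A comparison in mmHg is therefore legitimate in its own right.
- *Nothing in the plan compares the arms relative to baseline.* The hypotension outcome includes the 30% fall. What is missing is a measure against the ±10% band.

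Whether percentage of reference should be the main scale is open to debate, since a ratio carries any measurement error in the reference value. Using reference SBP as a covariate is not contentious.

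**Conclusion.** The point holds as a minor matter of precision and interpretation on a secondary process measure. Without reference SBP the GEE comparison is valid and unbiased, but its standard error would be about 2.1–3.0 mmHg where about 1.3 mmHg is attainable, that is 2.5 to 5 times the variance. These figures rest wholly on the assumed spread and separation of SBP. The statement that a difference in mmHg cannot be read against the ±10% band needs no assumed figure; it follows from how the target is defined. The primary outcome, the sample size and the validity of the trial's main conclusion are unaffected.

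**What to change.** In Statistical analysis, state that the GEE for SBP over time includes arm, time, arm-by-time interaction and reference SBP as a covariate. Add that SBP as a percentage of reference (SBP divided by reference SBP, times 100) will be shown as a companion analysis, so that the separation can be read against the ±10% band. The covariate supplies the precision and the companion analysis supplies the reading against the target.

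The cost is one or two sentences and one derived variable from values already recorded. No procedure, sample size or primary analysis changes. Recruitment is described as ongoing, so the wording can be settled before the data are analysed. If an unseen analysis plan already contains these terms, nothing more is needed than to make the article agree with it.
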